## Abstract

**Objectives:**

To assess, in terms of self-efficacy in weight management, the effectiveness of the SLIM lifestyle intervention among overweight or obese women during pregnancy and after delivery, and further to exploit machine learning and event mining approaches to build personalized models. Additionally, the aim is to evaluate the implementation of the SLIM intervention.

**Methods:**

This prospective trial, which is a non-randomized, quasi-experimental, pre-post intervention, includes an embedded mixed-method process evaluation. The SLIM Intervention is delivered by public health nurses (n = 9) working in maternity clinics. The public health nurses recruited overweight women (n = 54) at their first antenatal visit using convenience sampling. The core components of the intervention i.e. health technology, motivational interviewing, feedback, and goal setting, are utilized in antenatal visits in maternity clinics starting from gestational week 15 or less and continuing to 12 weeks after delivery. Mixed effect models are used to evaluate change over time in self-efficacy, weight management and weight change. Simple mediation models are used to assess calories consumed and moderate to vigorous physical activity (MVPA) as mediators between self-efficacy and weight change. Signal processing and machine learning techniques are exploited to extract events from the data collected via the Oura ring and smartphone-based questionnaires.

**Discussion:**

The SLIM intervention was developed in collaboration with overweight women and public health nurses working in maternity clinics. This study evaluates the effectiveness of the intervention among overweight women in increasing self-efficacy and achieving a healthy weight; thus, impacting the healthy lifestyle and long-term health of the whole family. The long-term objective is to contribute to women’s health by supporting weight-management through behavior change via interventions conducted in maternity clinics.

**Trial registration:**

The trial was registered at the Clinicaltrials.gov register platform (ID NCT04826861) on 17 March 2021.

## Introduction

Obesity has nearly tripled during the last few decades [1] and has become a global health concern; this trend can also be seen among pregnant women. In Finland, for example, 41.7% of pregnant women were overweight (BMI ≥25) and 17.6% were obese (BMI ≥30) in 2019 [2]. Correspondingly, almost a third (29%) of pregnant women in the US were obese in 2019 [3]. Maternal overweight increases the risks for obstetric complications and newborn mortality and morbidity, such as gestational diabetes, obstetric intrapartum complications, and caesarean section, macrosomia and stillbirths [2, 4, 5]. Consequently, preventing and decreasing obesity in pregnant women is essential to improve the health of future generations. Pregnancy is an exceptional period in a women’s life; there is often a shift in attitude and a spontaneous change in positive health behaviors, making women more receptive to advice on nutrition and physical activity. It is crucial to support their willingness to change health behaviors and encourage the motivation to take care of their own and their unborn child´s health. Healthy lifestyle behaviors adopted during pregnancy are also likely to have positive impacts on women’s health after pregnancy [6].

Previous behavioral lifestyle interventions focusing on a healthy diet and physical activity have succeeded in reducing gestational weight gain and improving pregnancy outcomes, for example, by reducing the number of macrosomia or caesarean sections. Further, some interventions have reduced neonatal respiratory distress syndrome and some interventions have also been associated with a reduction of postnatal depression [7–10]. However, these interventions have focused on single outcomes, and are not established as part of maternity care. In addition, counseling that focuses on giving general information on healthy diets and exercise is not usually effective; instead, the focus should be placed on individual barriers and challenges. Furthermore, weight gain may not be the most optimal parameter to focus on during pregnancy because obesity is a sensitive and stigmatizing subject, which is often found to be difficult to discuss with pregnant women. Hence, the focus of interventions should be on health promotion instead of weight loss [11]. Overall, there is a clear necessity for innovative and cost-effective lifestyle interventions to promote weight-management and health outcomes [8, 12].

As an alternative to teaching obese pregnant women to eat healthily and increase their activity the target should be to enhance the individual’s self-efficacy, which is a crucial psychosocial factor underpinning change in behavioral practices [13, 14]. In addition, self-efficacy has been shown to be a strong predictor of health behaviors and weight control, including physical activity and dietary intake and therefore, body weight [15, 16]. More comprehensive research is required to investigate methods of incorporating improvement in the self-efficacy of overweight women during pregnancy and the postpartum period. These methods would need to help in overcoming barriers to weight management and provide the means to implement an optimal weight-management intervention. E-Health applications have been shown to be effective alternatives to standard practice; these apps and exercise programs supporting weight management have indicated a tendency, for example, toward less gestational weight gain, and an increase in step [17, 18]. In addition, continuous monitoring has been shown to be a good method for women and their health care professionals to create personalized interventions that minimize weight gain and help women to adopt healthy lifestyles during pregnancy.

Pregnant women meet health care professionals regularly, which enables the development of continuous collaboration and support between healthcare professionals and pregnant women. Therefore, pregnancy is an optimal period for establishing weight management interventions, which are most effective when introduced as part of routine antenatal care [11, 19]. Previous interventions have not been implemented as apart of maternity care. To implement interventions effectively the focus should be on the needs of overweight women and the promotion of self-efficacy. In the context of pregnant women, it is therefore important to understand the barriers and enablers that can prevent or help achieve changes in health outcomes. Given the importance of effective weight-management interventions, there is a need to develop feasible implementation strategies to support the adoption of interventions in real life settings. Local content and tailored implementation strategies could be crucial to bridging the gap between implementation research and clinical practice [20, 21].

The focus of the SLIM intervention is on supporting and refining existing antenatal services, which have proven to be effective [22]. The SLIM intervention offers health data to be utilized in maternity care: public health nurses (PHN) give feedback and set goals in collaboration with overweight pregnant women using motivational interviewing methods. The SLIM intervention has been initiated in close collaboration with the end users, i.e. overweight pregnant women and PHNs working in maternity clinics, and its target is to enhance the participants’ self-efficacy and to promote their weight management. The effectiveness and implementation will be evaluated in routine maternity care using implementation framework [23].

### Aims

The first aim of this study is to assess the effectiveness of the SLIM intervention in terms of improving self-efficacy in eating and physical activity (primary outcome) and preventing excessive gestational weight gain (secondary outcome). Further, the events and patterns from the collected health parameters during pregnancy and the postpartum period will be extracted and the variations and trends will be tracked to build personalized models. The second aim is to evaluate the implementation of the SLIM intervention with regard to perceived fidelity, acceptability, appropriateness, and feasibility among PHNs and women with overweight or obesity.

## Methods

### Design and settings

This is a prospective intervention trial that is non-randomized and quasi-experimental (pre-post) and includes an embedded mixed-method process of evaluation. The study will be conducted in two public maternity clinics located in four municipalities in the Hospital District of Southwest Finland between April 2021 and May 2023.

In Finland, pregnant women receive free care from public maternity clinics as part of the general health care arranged by municipalities. Women usually visit a PHN a total of 10–11 times during pregnancy and after delivery. Public health nurses in maternity clinics provide support with particular attention to the promotion of welfare and health. This includes guidance and support regarding sleep, physical activity and nutrition and food recommendations for pregnant and breastfeeding mothers [24]. With reference to maternal weight gain during pregnancy, PHNs also provide advice on weight management based on pre- pregnancy BMI [6].

#### Target group 1: Overweight women

Overweight women (n = 54) were recruited at their first antenatal visit using convenience sampling. The power analysis was calculated based on two scales, self-efficacy in eating (WEL) and physical activity (PASE). Calculations were done with one sided t-tests with an effect size of 0.50, a power level of 0.80 and a significance level of 0.05. A 20% loss was included in the calculation. Based on both scales, a sample of 54 overweight pregnant women was needed to detect the difference in changes in eating self-efficacy or self-efficacy in physical activity.

Women were eligible for inclusion if they were 1) pregnant ≤15 weeks of gestation, 2) ≥18 years of age and 3) overweight or obese (BMI ≥ 25kg/m2) and 4) had adequate language skills in Finnish. Women were excluded if they 1) did not have a mobile device to download applications and synchronize data, 2) had a diagnosis of severe mental illness, 3) were diagnosed diabetes type 1 before pregnancy and/or 4) had mobility limitations.

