The strengths of this study can be found in the theory-based development of the trial and also in including the end users in the intervention and trial development. A potential limitation of this study is the selection bias in participant recruitment and retention; as weight is a sensitive subject and participation is voluntary, it is expected that those overweight women willing to participate are already motivated to make behavioral change, and this will probably result in more positive findings. There will most likely be a number of overweight women that would benefit from this intervention, but did not want to participate, e.g., women with mental problems that are often related to being overweight; these women would also be more challenging to motivate into behavioral change. Another limitation is our relatively long follow-up time, which might result in high drop-out rates. However, possible drop-outs were considered in the power calculations so that the results reached the necessary sample size.

The SLIM intervention has a strong potential to increase overweight pregnant women’s self-efficacy, limit excessive gestational weight gain and also prevent postpartum weight retention. This may impact the lifestyle and long-term health of these women as well as their families. Our long-term aim is to involve communal care maternal clinics in promoting women’s healthy lifestyle, improved self-efficacy, and healthy weight management.

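### The stated power inputs give 34 women under a paired t-test, not 54; the basis for 54 needs restating, though the sample size can stand

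*Protocol article*

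**What the plan says.** The sample size is justified in the protocol article under Methods, Target group 1: Overweight women. It covers two scales, WEL for eating and PASE for physical activity, which are the primary outcomes. The article states that "Calculations were done with one sided t-tests with an effect size of 0.50, a power level of 0.80 and a significance level of 0.05" and that a 20% loss is already included. It concludes that "a sample of 54 overweight pregnant women was needed to detect the difference in changes in eating self-efficacy or self-efficacy in physical activity".

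The design is given under Design and settings: "This is a prospective intervention trial that is non-randomized and quasi-experimental (pre-post". No comparison group is described anywhere. The article does not say which kind of t-test was used, which SD the effect size is scaled to, or what pre-post correlation was assumed. It mentions no division of the significance level between the two scales.

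The Discussion returns to the calculation once, to say that "possible drop-outs were considered in the power calculations so that the results reached the necessary sample size".

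**The concern.** The article gives every input that a simple paired calculation needs, together with the result, and the two do not agree. The gap between 34 and 54 is too large for rounding or a difference between programs.

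This is the trial's only power statement and it serves both primary outcomes. A reader cannot tell what effect 54 women were meant to detect, or whether 80% is the power of the trial as enrolled. The conclusion adds to the doubt, because it speaks of a difference between changes. That is the language of comparing two groups, and this trial has one.

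**Working it through.** **Inputs**, all from Target group 1 unless noted:
- Test: "Calculations were done with one sided t-tests"
- Effect: "an effect size of 0.50"
- Power: "a power level of 0.80"
- Alpha: "a significance level of 0.05", with no split stated
- Loss: 20%, included in the total
- Design: single group, pre-post (Design and settings)

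**Step 1. Attempt to reproduce 54.** For a one-sample t-test on the change, with d the mean change divided by the SD of the change,

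power = P(T > t(0.95; n − 1)), where T is noncentral t with n − 1 df and noncentrality d√n.

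- n = 26: noncentrality 0.50 × √26 = 2.550, power 0.798
- n = 27: noncentrality 0.50 × √27 = 2.598, power 0.812

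So 27 completers are needed. Allowing for loss, 27/(1 − 0.20) = 33.75, or 34 enrolled. Multiplying instead gives 27 × 1.2 = 32.4, or 33. Neither is 54.

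**Step 2. Other readings at 80% power and d = 0.50.**

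| Reading | Completers | Enrolled (n/0.8) |
|---|---|---|
| Two-sided 0.05 | 34 | 43 |
| Wilcoxon, lower-bound efficiency 0.864, one-sided 0.05 | 27/0.864 = 31.25 | 40 |
| Joint 80% power on two independent scales, one-sided 0.05 | 35 | 44 |

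None gives 54.

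**Step 3. What does give 54, or close to it.**
- Power 0.95, one-sided 0.05: 45 completers, and 45 × 1.2 = 54. This changes the stated power and inflates by multiplication.
- Power 0.90, two-sided 0.05: 44 completers, and 44/0.8 = 55. This changes two stated inputs.
- Two-sided 0.025 at 80% power: 41 completers, and 41/0.8 = 51.25, or 52. This changes the sidedness and the alpha.
- Doubling the completers: 2 × 27 = 54. The article does not say this was done.
- Effect size on the raw SD. With equal SDs before and after and correlation r, the effect in SDs of the change is 0.50/√(2(1 − r)). Every stated input is kept, but r has to be supplied:

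| r (assumed) | Effect in SDs of the change | Completers | Enrolled |
|---|---|---|---|
| 0 | 0.354 | 51 | 64 |
| 0.16 | 0.386 | 43 | 54 |
| 0.17 | 0.388 | 43 | 54 |
| 0.20 | 0.395 | 41 | 52 |
| 0.30 | 0.423 | 37 | 47 |
| 0.50 | 0.500 | 27 | 34 |

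**Step 4. What 54 enrolled delivers.** 54 × 0.8 = 43.2, so 43 completers. With 0.50 in SDs of the change, the noncentrality is 0.50 × √43 = 3.279. Power is 0.943 at one-sided 0.05 and 0.893 at two-sided 0.05. One-sided power of 80% is reached at an effect of about 0.385 SD.

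With 0.50 on the raw SD, one-sided power at 43 completers is 0.74 at r = 0, 0.80 at r = 0.16, 0.86 at r = 0.30 and 0.94 at r = 0.50.

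**The case against.** The strongest reply is that the article never defines its effect size. If 0.50 is scaled to the raw SD and the pre-post correlation is 0.16 to 0.17, all the stated inputs hold and the answer is exactly 54 with 80% power. This stands, so it would be wrong to say that 54 arises only by altering a stated input. It does not remove the point, because the article gives no correlation and the match is narrow: 0.20 already gives 52 and 0.50 gives 34.

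A second reply is that the error is harmless. On the SD-of-change reading, 43 completers exceed the 27 needed, so the Discussion's remark that drop-out was allowed for is true in substance. This also stands, and it is why the point is a correction to the reporting and not a threat to the trial.

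A reader might take the wording about a difference between changes literally and infer a two-group trial that is badly underpowered. The documents do not support that. The design is pre-post and no comparator appears, so the phrase is most plausibly loose wording for change over time.

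A reader might also infer a proven surplus of power that ought to be spent on a two-sided test with alpha split over the two scales. The surplus depends on the effect-size definition, and the article states one-sided 0.05. Changing that is a separate design choice.

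**Conclusion.** The point holds in a limited form: 54 does not follow from the stated inputs under the paired t-test that suits this design. Those inputs give 27 completers and 34 enrolled, so 54 is about 59% higher (54/34 = 1.59). Reaching 54 takes a changed input or an unstated one, and the article does not show which was used.

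The size of the misstatement depends on one assumption. If 0.50 is in SDs of the change, the power belonging to 54 enrolled is about 94%, not 80%, and the effect detectable with 80% power is about 0.385 SD, not 0.50. The error is then conservative. If 0.50 is on the raw SD, the stated 80% is right only near a correlation of 0.16.

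It would go too far to call 54 itself wrong, or to say that the trial was sized inadequately. What is established is that the trial's only power statement cannot be reproduced as written. It should be fixed.

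**What to change.** Keep 54 and rewrite the power paragraph under Target group 1. If the effect size is in SDs of the change, it could read: 'Single-group paired t-test of mean change from baseline; 54 enrolled, 20% loss, 43 completers; power about 94% per scale for an effect of 0.50 SD of the change at one-sided 0.05 (89% at two-sided 0.05).'

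If another definition was used, state it together with the pre-post correlation that yields 54. In either case:
- name the type of t-test and say how the two scales were handled;
- replace the wording about a difference between changes with 'mean change from baseline';
- compute the allowance for loss as n/(1 − loss).

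Moving to a two-sided test with alpha divided between the scales is optional and not part of this correction.

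The cost is one paragraph, with no additional participants and no change to the analysis.

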#### Target group 2: Public health nurses

All PHNs (n = 9) working in selected maternity and child health clinics were eligible for the study. The researcher applied for approval from the Nursing Director of the health center and contacted the PHNs via e-mail and scheduled meetings. Public health nurses were already recruited in the intervention development phase.

### Intervention

The SLIM intervention is targeted at overweight pregnant women with a goal to improve their self-efficacy in weight management. The intervention is being delivered by PHNs working in maternity clinics (Fig 1).

**Fig 1 pone.0279696.g001:**
[figure not shown]
SPIRIT schedule presenting participant timeline. ^a^ Pregnancy week less than 15. ^b^ Pregnancy week 34.

### Development of the intervention

The Grol and Wensings [25] five-step implementation-of-change model guided the development process (Fig 2) and overweight pregnant women and PHNs working in selected maternity clinics participated in the development of the intervention.

**Fig 2 pone.0279696.g002:**
[figure not shown]
The development process of the weight management intervention for overweight pregnant women.

**Step 1**: Development of proposal/targets for improvement were conducted based on previous literature of weight management interventions, national guidelines and local patient record data. Data on pregnancy and delivery, BMI before pregnancy and after delivery, breastfeeding information and depression scores were obtained from the electronic patient records collected in 2018 at one maternity clinic. In order to establish a detailed understanding of the weight management problem, these acquired statistics for the region’s overweight women and the information on obesity and weight management interventions based on the literature [9, 26, 27] were introduced to PHNs (n = 8) and their Nursing Director. A total of 84 pregnant women attended pre-pregnancy care in maternity clinics in 2018 in the area of the two municipalities and the majority (67.9%) were overweight or obese.

**Step 2**: The analysis of performance, the target group and settings were examined through individual interviews with overweight women (n = 11) and focus group interviews with PHNs (n = 5) [28]. Weight management behaviors were identified from the perspective of the maternity care professionals and the overweight and obese women with the help of the Behaviour Change Wheel (BCW) [29]. The results revealed that interventions should offer clear advice and non-judgmental support during pregnancy and after delivery by targeting women’s capabilities, opportunities, and motivation. In addition, health technology could be a valuable component of the intervention, as well as an implementation strategy that would provide ways to approach this topic and support women in maternity clinics. To assess the usability of health technology and wearable devices as a potential intervention element, a purposive sample of overweight and obese women (n = 7) and PHNs (n = 6) wore smart wearables for seven consecutive days. Participants completed a semi-structured diary each day to assess the comfort and usability of the devices and the application. Participants preferred the Oura Smart Ring to the Samsung smart watch, as it was comfortable to wear and had a beautiful appearance.

**Step 3**: Development and selection of strategies and measures for practicing change were conducted by linking identified target behaviors and determinants of the national guidelines to the intervention components. Previously identified weight management target behaviors [28] were mapped to the matrix of BCW (S1 Table). These results were presented to the PHNs and based on their discussions and consensus the most helpful elements for their clinical work in maternity clinics were chosen. These elements were *health technology* to support self-monitoring and goal setting, *motivational interviewing*, *feedback and goal setting* to enhance the motivation to improve self-efficacy in weight-management. A template for the intervention description and replication (TIDieR) was used as a guideline to improve the comprehensive reporting of the intervention (S2 Table).

**Step 4**: Development, testing and execution of the implementation plans were conducted in collaboration with PHNs. Meetings were conducted with PHNs to present a summary of the previous phases of the study and the interventions core components based on TIdieR. In addition, more information on specific requirements as regards the implementation of the intervention were collected from PHNs; these were used to choose strategies to support the implementation of the SLIM intervention in the daily work of PHNs. The following are the multi-faceted implementation strategies which were chosen and classified using the Expert Recommendations for Implementing Change (ERIC) [30]: *educational meetings*, *educational materials*, *local opinion leaders*, *mandate change and reminders*. Before the recruitment of the overweight pregnant women, all eligible PHNs were invited to attend *educational meetings*, which involved one-hour sessions in scheduled appointments and were delivered by the researchers. In addition, *educational materials* developed by researchers were delivered during the meetings. During the data collection period, researchers scheduled workshops with maternity clinic nurses every six months. *The local opinion leaders* were selected from among the PHNs, one in each maternity clinic. These leaders provided information, and played an important role in liaising with other nurses delivering intervention and also influenced their participation. *Mandate change*, requiring leaders to declare the importance of the innovation and their determination to have it implemented was conducted every two months in regular meetings of the maternity clinic staff. *Reminders* were sent to PHNs via email every month. To promote adherence to the intervention nurses were encouraged to contact the researchers if any issues related to the implementation of the intervention occurred. The specifications of the implementation strategies are presented in the supplementary material (S3 Table) [30].

**Step 5**: The evaluation plan for intervention implementation is presented below and in Fig 1.

